## Abstract

**Background:**

Half of all lower limb deep vein thrombi (DVT) in symptomatic ambulatory patients are located in the distal (calf) veins. While proximal disease warrants therapeutic anticoagulation to reduce the associated risks, distal DVT often goes untreated. However, a proportion of untreated distal disease will undoubtedly propagate or embolize. Concern also exists that untreated disease could lead to long-term post thrombotic changes. Currently, it is not possible to predict which distal thrombi will develop such complications. Whether these potential risks outweigh those associated with unrestricted anticoagulation remains unclear. The Anticoagulation of Calf Thrombosis (ACT) trial aims to compare therapeutic anticoagulation against conservative management for patients with acute symptomatic distal deep vein thrombosis.

**Methods:**

ACT is a pragmatic, open-label, randomized controlled trial. Adult patients diagnosed with acute distal DVT will be allocated to either therapeutic anticoagulation or conservative management. All patients will undergo 3 months of clinical and assessor blinded sonographic follow-up, followed by 2-year final review. The project will commence initially as an external pilot study, recruiting over a 16-month period at a single center to assess feasibility measures and clinical event rates. Primary outcome measures will assess feasibility endpoints. Secondary clinical outcomes will be collected to gather accurate data for the design of a definitive clinical trial and will include: (1) a composite endpoint combining thrombus propagation to the popliteal vein or above, development of symptomatic pulmonary embolism or sudden death attributable to venous thromboembolic disease; (2) the incidence of major and minor bleeding episodes; (3) the incidence of post-thrombotic leg syndrome at 2 years using a validated screening tool; and (4) the incidence of venous thromboembolism (VTE) recurrence at 2 years.

**Discussion:**

The ACT trial will explore the feasibility of comparing therapeutic anticoagulation to conservative management in acute distal DVT, within a modern cohort. We also aim to provide contemporary data on clot propagation, bleeding rates and long-term outcomes within both groups. These results will inform the conduct of a definitive study if feasibility is established.

**Trial registration:**

Current Controlled Trials ISRCTN75175695

## Background

Venous thromboembolic (VTE) disease is an international, topical and costly healthcare burden. Incidence rates are equivalent to that of stroke within the western hemisphere [1] and disease consequences can be as severe. Recent studies addressing prognosis provide a stark reminder of continuing poor outcome, quoting a 15% mortality rate at 3 months post diagnosis for VTE involving the pulmonary vascular tract [2]. Outcome from VTE confined to the lower extremities fares little better, with a reported short-term all-cause mortality between 7% and 15% [3]. Observational data suggests reduced survival compared to control subjects after first episode of symptomatic deep vein thrombosis. This trend has been shown to persist for up to 8 years post diagnosis [4]. Clinical research demonstrating poor outcome has led to a national focus on early diagnosis and active prevention, with the creation of guidelines from both the UK Health Technology Assessment (HTA) group and the National Institute of Clinical Excellence (NICE) within the last decade [5,6].

Despite the large body of research on VTE, controversy still remains regarding many aspects of therapeutic clinical practice. One such area is that of distal deep vein thrombosis (DVT), a condition previously thought to be of limited clinical significance. There are multiple epidemiological studies suggesting distal thrombi constitute approximately 50% of objectively diagnosed lower limb disease in symptomatic ambulatory patients [7-9]. This proportion may be even higher in asymptomatic disease or hospitalized patients [10]. However, the benefits of intervention in distal disease remain poorly researched, with conflicting international guidance on investigation and treatment.

Some authors question the ability of ultrasound to diagnose distal DVT. Indeed, recent meta-analyses have consistently failed to show a pooled sensitivity for detection of distal thrombosis by ultrasound any higher than 75% [11,12]. This failing could well be related to the potential pitfalls of the current gold standard: contrast venography has been noted as a potential cause of DVT and has many additional caveats, including extravasation reactions, technical limitations and variable interobserver reliability [13,14]. Despite these failings, many clinicians cite the poor sensitivity data and choose to base their management strategies on serial compression ultrasound of the thigh, avoiding the distal veins altogether. In the absence of sonographic progression to proximal veins after 7 days, the presence of distal disease is presumed to be clinically irrelevant. Recent well conducted studies report a non-significant difference in 3-month VTE event rates between patients randomized to be investigated by serial or complete leg ultrasound in suspected DVT [15,16]. The British Society of Haematology endorse this approach to suspected lower limb VTE in a national guidance document [17]. Thus, many clinicians withhold anticoagulation after serially negative proximal ultrasound.

Conversely, it is also well recognized that a proportion of untreated distal disease will propagate, embolize and/or lead to chronic venous pathology. Current estimates of proximal propagation in untreated patients range between 0% and 29%, with some untreated patients developing pulmonary emboli during short-term follow-up [18]. The most relevant studies assessing complication rates in untreated patients can be seen in Table 1[19-25]. There have also been previous reports of fatal pulmonary embolism occurring within the 7 days after initial negative proximal ultrasound in suspected disease [26]. The potential to cause post-thrombotic syndrome (PTS) is valid but as yet unquantified [27,28]. These sequelae prompt some clinicians to advocate standard therapeutic anticoagulation for all. Several international organizations endorse this approach when diagnosis is clarified [29-31].

**Table 1 T1:** Prospective studies assessing complication rates in untreated distal deep vein thrombosis (DVT) patients

Author/year	Population	Sample size	Diagnostic method	Duration of follow-up for primary endpoint	VTE complication rate
Schwarz et al. 2010 [22]	Low-risk ambulatory patients with isolated calf muscle thrombus	53	CUS	3 months	2/53 = 3.77%

Palareti et al. 2010 [21]	Symptomatic outpatients	65	CUS	3 months	5/64 = 7.8%

Macdonald et al. 2003 [19]	Mostly symptomatic surgical and medical inpatients (68.6%) with isolated calf muscle vein thrombus	135	CUS	3 months	4/135 = 3%

Schwarz et al. 2001 [23]	Symptomatic outpatients with isolated calf muscle vein thrombosis	32	CUS	3 months	8/32 = 25%

Lohr et al. 1995 [18]	Mostly symptomatic surgical and medical inpatients (59.4%)	192	CUS	4 weeks	21/169 = 12.4%

Oishi et al. 1994 [20]	Asymptomatic postoperative total hip replacement/total knee replacement patients	41	CUS	12 months	7/41 = 17.1%

Lagerstedt et al. 1985 [17]	Symptomatic medical patients	28	Isotopic uptake confirmed by ascending phlebography	90 days	8/28 = 29%

CUS = compression ultrasound; VTE = venous thromboembolic complication rate: this refers to ascending proximal extension of the thrombus to the popliteal vein or development of symptomatic pulmonary embolism, except for the study by Schwarz et al. [23]. In this trial, patients were commenced on therapeutic anticoagulation if the distal thrombus propagated to any of the deep calf veins. Many cases were therefore treated prior to potential popliteal extension.

It remains unclear whether the benefits of treatment outweigh the potential harms. The only randomized trial comparing conservative management to standardized oral anticoagulation in distal DVT was performed by Lagerstedt et al. in 1985 [19]. A total of 51 participants were included. The authors demonstrated a 29% 3-month recurrence rate and a 32% 1-year recurrence rate for conservatively managed patients with distal DVT. The incidence of recurrence in warfarinized patients was significantly lower, 0% at 3 months and 4% at 1 year. The results from this trial have been much debated, with many authors highlighting the small sample size, composite diagnostic standards and unequal baseline characteristics between groups [32].

Recent studies using ultrasonography to detect recurrence or propagation have failed to replicate Lagerstedt et al.'*s *data. Using a limited treatment regimen of reduced dose heparin for 4 weeks only, Parisi et al. demonstrated a 2.9% propagation rate at 3-month follow-up [33]. The blind, prospective CALTHRO study has recently reported low rates of venous thromboembolism/recurrence in untreated patients at 3 months, noting an event rate of 7.8% (95% CI 3% to 17%) [23]. Schwarz et al. have demonstrated further reduced event rates when selecting out low-risk distal DVT for conservative treatment, with propagation in only 3.7% of untreated patients [24]. However, no study has attempted to definitively answer the question by performing an adequately powered prospective randomized controlled trial (RCT). This is highlighted by a recent meta-analysis that notes the heterogeneity of trial data and fails to provide a robust conclusion, despite analyzing data from over 450 patients [34]. Equipoise remains, perhaps best highlighted by recent European research noting the profound and continuing regional variability in diagnostic and therapeutic approach to distal DVT [35]. Recent articles have highlighted the need for robust evidence and called urgently for further prospective RCT data to inform clinical decision making [32,36,37].

We designed a trial to examine the feasibility of testing the applicable null hypothesis: that therapeutic anticoagulation for 3 months confers no significant clinical benefit in the management of acute symptomatic distal DVT, when compared to conservative treatment alone.

## Methods

### Study aims

The Anticoagulation of Calf Thrombosis (ACT) trial aims to compare the incidence of venous thromboembolic complications in patients with distal deep vein thrombosis treated with either standard therapeutic anticoagulation or conservative management.

### Study design and setting

The study will be initially conducted as a prospective, randomized, open-label, pragmatic, controlled trial within the Emergency Department (ED) at Central Manchester University Hospitals NHS Foundation Trust. The ED has an average annual attendance figure of 110,000. The trial will begin as an external pilot project, recruiting distal DVT patients over a 16-month period at a single center to assess feasibility and gather accurate clinical outcome data. A study process flow chart is given in Figure 1.

**Figure 1 F1:**
[figure not shown]
**Summary of trial design/patient flow**. Proximal DVT relates to acute thrombotic disease above the level of the trifurcation of the popliteal vein. Chronic DVT relates to any reported thrombosis detected on prior documented ultrasound, previously treated, or with chronic appearance on contemporary ultrasound exam. DVT = deep vein thrombosis.

### Ethical considerations

Ethical approval for this study has been obtained from the North West Greater Manchester Central Research Ethics Committee (ref: 10/H1008/97) as a Controlled Trial of an Investigative Medicinal Product (CTIMP). The Medicines and Healthcare products Regulatory Agency (MHRA) have granted clinical trial authorization. A Data Safety and Monitoring Board (DSMB) including a leading expert in thrombosis/hemostasis will be convened to evaluate data and comment on safety within the trial. A Trust Steering committee will oversee local trial conduct and governance. The study is subject to all ongoing NHS Research and Development governance checks regarding CTIMP projects.

### Study interventions

Patients randomized to trial group A will receive immediate therapeutic anticoagulation with initial daily administration of subcutaneous low molecular weight heparin (LMWH), followed by 3 months oral standard NHS anticoagulant pharmacotherapy. Pending UK adoption of novel agents, oral anticoagulation will be achieved with warfarin targeted to an international normalized ratio (INR) of 2.5 (range 2.0 to 3.0). Patients will be monitored by a dedicated anticoagulant clinic at the study site and seen at regular intervals for INR testing. Methods for adjusting warfarin dose and maintaining target INR will be at the discretion of the anticoagulant clinic service. Compliance will be evaluated within treatment groups. Group A patients will also receive grade 2 compression hosiery fitted externally through the orthotics department.

Group B trial patients will receive symptomatic treatment only, in the form of simple analgesia and fitted grade 2 compression hosiery.

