### Blinding

This is an open-label study. Although previous trials have used 'sham' anticoagulant clinics we feel use of placebo and frequent hospital visits to maintain blinding would be potentially unethical and deleterious to recruitment. Complications in the context of warfarinization also need urgent treatment and an unblinding protocol would naturally delay this.

All ultrasonographers will be blinded to allocation for repeat scans. Clinical outcome measures are primarily objective, which should minimize the risk of measurement bias.

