### Patient follow-up procedures

Patients will return at 7 and 21 days for follow-up duplex CUS and clinical review. Vascular radiology technicians will be blinded to treatment allocation for all scans. Propagation of DVT to the level of the popliteal vein (above the trifurcation) at any point post randomization will be considered as proximal extension and result in immediate therapeutic anticoagulation. Patients will be clinically reviewed and outcome data collected when they attend for repeat CUS. Worsening symptoms in the context of non-propagation above the trifurcation will be assessed carefully and further investigations will be dictated by clinical need.

At the end of the 3-month treatment period all subjects will be followed up via medical record review and structured telephone interview. An ED appointment will be arranged if any queries or clinical concerns persist. All patients will be encouraged to continue wearing compression stockings daily for 2 years, as per current evidence [38]. Suspicion of pulmonary VTE at any stage will be investigated as per current practice and confirmed by Prospective Investigation Of Pulmonary Embolism Diagnosis (PIOPED) reported V/Q scan or computed tomography (CT)-pulmonary angiography [39]. Any patient diagnosed with pulmonary VTE will receive immediate therapeutic anticoagulation as per current practice. Out of normal working hours, patients will be advised to attend the ED with any concerns, where a protocol for investigation of suspected pulmonary embolism in ambulatory patients is already standard practice.

Final clinical review and data collection will occur at 2 years post inclusion, regarding the incidence and severity of post thrombotic syndrome and the incidence of DVT recurrence in all patients. The diagnosis and severity of PTS will be assessed using the standardized scoring system validated by Villalta et al. [40].

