### Patient outcome measures

As an external pilot study, the primary endpoints for the trial will constitute measures of feasibility only. A successful pilot RCT seeks to collect data regarding process, resources, management and scientific data [41]. Feasibility outcomes have been designed to reflect this. Clinical measures of treatment effect and safety will be recorded as secondary outcomes, in order to inform further sample size calculations and data inference for potential future multicenter research.

Primary feasibility outcomes are: incidence of the index condition, the proportion of eligible patients within the screening cohort, recruitment rate for those deemed eligible, allocation crossover and short-term compliance with the study protocol.

Secondary outcomes are: combined incidence of thrombus propagation to the popliteal vein, DVT recurrence, development of pulmonary embolism or VTE related sudden death during the 3-month intervention period; incidence of major and minor bleeding episodes during the 3-month treatment period; incidence of post-thrombotic leg syndrome at 2 years; and incidence of VTE recurrence at 2 years.

Outcome measures will be defined using the following tools: DVT recurrence or development of pulmonary embolism will be confirmed by objective diagnostic criteria, either via repeat CUS in the presence of worsening symptoms or PIOPED reported ventilation-perfusion scan or CT pulmonary angiogram in the presence of new chest symptoms [39]. Any cases of sudden death during the interventional phase of the trial will be assessed by a panel of experts blinded to treatment allocation, including a Professor of Emergency Medicine, Consultant Hematologist and Consultant Respiratory Physician. A consensus decision will be required regarding VTE as the principal cause of death.

Major bleeding episodes will be defined as standardized in 2005 by Schulman et al.: clinically overt and associated with a fall in hemoglobin of 20 g/l, resulting in the need for transfusion of two or more units of red cells, involving a critical site, or fatal [42]. Minor bleeding episodes will be subcategorized as per Schulman et al. in 2009 into clinically relevant, or nuisance bleeding [43].

Post-thrombotic syndrome will be diagnosed and numerically graded using the validated and internationally adopted Villalta scale [40].

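### Only group A attends an anticoagulant clinic, so the between-arm comparison of minor bleeding is at risk of unequal ascertainment; recording the source of each bleed and adding a common-contacts comparison would show how much

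*Protocol article*

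**What the plan says.** Under Study interventions, the paragraph on group A states: "Patients will be monitored by a dedicated anticoagulant clinic at the study site and seen at regular intervals for INR testing". The next paragraph says: "Group B trial patients will receive symptomatic treatment only, in the form of simple analgesia and fitted grade 2 compression hosiery". No clinic attendance is described for group B, and the Blinding section explains that sham clinics were considered and rejected on ethical and recruitment grounds.

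Patient follow-up procedures describes outcome collection without distinguishing the arms. "Patients will return at 7 and 21 days for follow-up duplex CUS and clinical review", and "Patients will be clinically reviewed and outcome data collected when they attend for repeat CUS". Then: "At the end of the 3-month treatment period all subjects will be followed up via medical record review and structured telephone interview". The article does not say which records are reviewed.

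The safety outcome under Patient outcome measures is the "incidence of major and minor bleeding episodes during the 3-month treatment period". Minor bleeding is split there into clinically relevant and nuisance events. The trial is open label. Blinded assessment is stated for the repeat scans and for sudden deaths, and none is stated for bleeding. On measurement bias, the Blinding section says: "Clinical outcome measures are primarily objective, which should minimize the risk of measurement bias". Statistical analysis compares secondary endpoints between arms with Fisher's exact test.

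**The concern.** The number of occasions on which a bleed can be mentioned and written down differs by arm. After day 21, group B has no scheduled contact until the 3-month interview. Taking 3 months as 90 days, that is 90 − 21 = 69 days. Group A has clinic attendances during that time, at a site whose notes a record reviewer could readily reach.

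A nosebleed or bruise mentioned at an INR visit may be documented in group A, while the same event in group B may be forgotten by the time of the interview. Objectivity of definition does not help here: an event can be classified without bias once reported and still be reported more often in one arm.

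The stake is the quality of the pilot's estimates. The abstract lists bleeding rates among the data the pilot is to supply, and the Discussion makes bleeding the harm to be weighed against prevention of thromboembolism. An excess of minor bleeding in group A would mix a real drug effect with extra detection, and the data as described could not separate the two.

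**Working it through.** The article gives no bleeding rate, no capture probability and no number of INR visits, so there is no stated figure to reproduce. What can be done is to compare the opportunities for capture and then show what follows under stated assumptions.

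**Opportunities for capture**

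| Source | Group A | Group B |
|---|---|---|
| Day 7 and day 21 review | yes | yes |
| 3-month structured interview | yes | yes |
| 3-month record review | yes, sources not stated | yes, sources not stated |
| Anticoagulant-clinic visits | yes, number not stated | none described |

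The shared schedule is equal. The difference lies in the last row and in whether it feeds the row above.

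**Formula.** Observed risk = true risk × capture probability. With the same true risk in both arms, the spurious risk ratio is (capture in A) ÷ (capture in B), and the spurious difference is true risk × (capture in A − capture in B).

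**Example (all three inputs assumed).** True minor-bleeding risk 15%, capture 90% in A and 60% in B.
- A: 0.15 × 0.90 = 13.5%. B: 0.15 × 0.60 = 9.0%.
- Ratio 13.5 ÷ 9.0 = 1.5. Difference 4.5 points.
- At 50 per arm (the target of 100, equal split assumed), this is 0.045 × 50 = 2.25 patients.
- 95% CI half-width: 1.96 × √(0.135 × 0.865/50 + 0.09 × 0.91/50) = 12.4 points.
- The two-sided Fisher test, by exact enumeration, rejects in 5.2% of such trials.

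**Range.** Capture in A fixed at 95%, 50 per arm, no true difference. Each cell gives the spurious difference in points, with the Fisher rejection rate in brackets.

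| Capture in B | Spurious ratio | True risk 5% | True risk 20% | True risk 30% |
|---|---|---|---|---|
| 95% | 1.00 | 0 (0.6%) | 0 (2.8%) | 0 (3.1%) |
| 80% | 1.19 | 0.75 (0.6%) | 3 (3.8%) | 4.5 (5.3%) |
| 65% | 1.46 | 1.5 (0.7%) | 6 (7.7%) | 9 (13.2%) |
| 50% | 1.90 | 2.25 (1.0%) | 9 (16.0%) | 13.5 (29.4%) |

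If capture is equal, the artefact is zero. If it is higher in A, the artefact runs against anticoagulation. A false positive test is rare at low risks and becomes noticeable only when minor bleeding is common and capture differs widely. The more general effect is a shifted estimate.

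**The case against.** The strongest reply is that both arms already have the same outcome collection: two reviews in person, then a structured interview and record review for everyone. The article nowhere says that bleeding is asked about at INR visits or that clinic notes are part of the review. The absence of sham clinics is a reasoned choice in a pragmatic trial. Question wording and form fields are details that an article may leave to the full protocol. Bleeding is a secondary outcome of a feasibility study whose success criteria do not mention it, and the composite proposed for the definitive trial contains only major bleeding.

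Most of this stands, and it limits the point. A reader might infer that the record review does draw on clinic notes and that the bleeding comparison is therefore biased. The text supports only that it may. A reader might also extend the point to major bleeding, but its criteria (a haemoglobin fall, transfusion, a critical site or death) make it much less sensitive to the number of contacts. Nor does the document support the idea that clinic visits prompt more investigation for thromboembolism in group A. Everyone is told to return with symptoms, and untreated patients in an open-label trial might equally be investigated more readily, so the direction is unknown.

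What remains is that the article offers a specific reassurance about measurement bias, and that reassurance does not reach an endpoint whose capture depends on being asked. The choice not to run sham clinics is defended on other grounds, without considering this consequence.

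**Conclusion.** The comparison of minor bleeding, above all nuisance bleeding, is at risk of differential ascertainment, in the direction of more events found in group A. This rests on three facts in the document: the clinic is attended by group A only, the 3-month record review is not limited by source, and no blinded bleeding assessment is stated. It also rests on one inference, that bleeds mentioned at the clinic are noted and then found.

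The size is unknown. The spurious ratios of 1.19 to 1.90 illustrate assumed capture rates and are not estimates. At 50 per arm, the 4.5-point example is well inside a confidence interval of about ±12 points. The feasibility conclusions are untouched and major bleeding is little affected. This is a cheap improvement to a secondary outcome, worth making because the pilot's bleeding rates are meant to inform the next trial.

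**What to change.** - **Patient follow-up procedures:** ask the same structured bleeding questions in both arms at day 7, day 21 and the 3-month interview, each time covering the period since the last contact. Record the source of every bleed (common contact, anticoagulant-clinic record, other record, patient-initiated attendance).
- **Patient outcome measures:** state that all major bleeds count whatever their source.
- **Statistical analysis:** report the between-arm comparison of minor bleeding twice, from all sources and restricted to events elicited at the common contacts. Show events found only in clinic records separately, as group A safety data.

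Both comparisons are needed. Using only the restricted one would drop documented group A bleeds that the patient did not recall, and could understate the harm of anticoagulation. If the two agree, ascertainment is an unlikely explanation for any excess. If they differ, the gap indicates how much of the excess depends on the extra sources. The restricted comparison does not remove differences in recall that come from patients knowing their treatment.

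The cost is one case report form field and one extra analysis, with no added visits or staff. The restricted group A rate will be somewhat lower than the all-source rate. Trial status reports 62 patients recruited by 15 January 2012. For them, the source could be filled in only where existing records show it, and the full change would apply to later patients and to the definitive trial.
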